#### Secondary outcomes

Health service utilisation (Client Service Receipt Inventory (CSRI)), social care (Adult Social Care Outcomes Toolkit, ASCOT) and physical and mental health components of the HIV PROM and EuroQol index score and visual analogue scale at 6 and 12 months. In addition, satisfaction with care will also be measured at each timepoint using the CARE measure.

### Data collection

Baseline demographic data will be collected including personal characteristics (age, gender, sex at birth, ethnicity) and social factors (marital status, employment status, residential status, formal education level, annual income) and comorbidities. Demographic data and patient record data capture for the enrolment and follow-up forms will be done by manual data keying or electronically. Manual data keying is performed in a secure online browser-based platform called REDCap. Electronic data capture entails local extraction of data from clinical electronic databases and will be stored securely on the UHSx systems, HIV drive. Only the research team (including research administrator) will have access to these data and will not be made available outside the team or institution.

Process data will be collected to understand intervention delivery and trial design appropriateness. For the Silver Clinic intervention, records pertaining to CGA date, recommendations and follow-up will be collected. For trial process data, trial screening, recruitment rates, participation at each time point and amount of missing data will be recorded.

Standardised clinical outcome measures that represent multiple health and healthcare service domains will be collected at baseline, week 26 and week 52 postrandomisation. The positive outcomes HIV PROM measures multidimensional symptoms and concerns for PLWH^34 35^; the EuroQol EQ-5D-5L measures health-related quality of life^36^; the ASCOT measures social care-related quality of life^37^; the CSRI measures services and support accessed^38^; the Consultation and relational empathy measure (CARE) is used to assess interpersonal quality of healthcare encounters^39^; the Fried Frailty Phenotype and FRAIL scale are used to assess physical frailty^33 40^; and the Timed Up and Go test to assess functional mobility and falls risk.^41^ Physical tests will be conducted by the researcher and questionnaires will be completed with support of the researcher.

### Nested qualitative interviews

OPWH will be recruited for qualitative interview via purposive sampling from within the RCT participants. OPWH will be purposively sampled by trial arm, age, gender, duration of HIV diagnosis, ethnicity, sexual orientation, living situation and frailty score, to ensure a maximum variation sample. Members of the study team will meet regularly to discuss ongoing recruitment and the characteristics of the recruited sample. This will allow for the identification of characteristics not yet included in the study and to purposively target these in subsequent participants, ensuring diversity in the overall sample.

A purposive sample of up to 15 participants from each arm of the trial will be interviewed on completion of trial participation to examine experiences of: recruitment to the trial, management of their priority concerns during the course of the trial, referral to the Silver Clinic, the description of CGA, experience of the Silver Clinic and perceived impact on priority outcomes (intervention arm only), satisfaction with care and acceptability of participating in an RCT of the Silver Clinic intervention for OPWH. Draft topic guides will be reviewed by PPI members. Face-to-face, telephone or video call interviews will be conducted by the research assistant and take place in a location of the participant’s choosing. Interviews will be digitally audiorecorded. Field notes will be used to record contextual factors, participant responses and personal reflections.

### Sample size

This is a feasibility trial, and therefore, not powered to test effectiveness of the intervention compared with standard treatment. However, data will be used to inform the sample size calculation for a future definitive trial. To precisely estimate the SD of the primary outcome for a future trial, a sample size of at least 35 participants per arm is recommended.^42 43^ Based on the local patient numbers (cohort of 2450; 54% over 50 years old), we anticipate recruiting 42 patients per arm, that is, 84 in all allowing for attrition of 15% to be achievable.

### Randomisation and blinding

After the baseline assessment, the research assistant will randomise participants using REDCap in a 1:1 allocation to receive either usual care (control arm) or referral to the Silver Clinic (intervention arm), stratifying one age (50–56, 66–80, 81–95 and 96–110) and sex to ensure a balanced sample in both arms. Clinicians delivering the intervention will be blinded to the screening and randomisation process as they will have no knowledge of when patients are screened for frailty nor have any influence on the randomisation process, minimising the possibility of selection bias.

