## Introduction

Of the people accessing HIV services in the UK, 39% are now aged 50 and over.^1 2^ People living with HIV (PLWH) over 50 appear to experience a disproportionate amount of comorbidities in comparison to their HIV negative counterparts, particularly in regard to geriatric syndromes, such as frailty and cognitive deterioration, which they experience at younger ages.^3 4^ Studies including a younger cohort of PLWH aged 50–64 demonstrate a frailty prevalence comparable to that of HIV negative cohorts aged 65 and older.^5^ As such, PLWH may not yet have reached the current UK recommended ages for frailty identification advocated in primary, secondary and community care settings.^6 7^ This coupled with the potential limited access to geriatric and other frailty services based on age alone, runs the risk of delayed identification of frailty and identification at a more severe stage where interventions may be less effective, resulting in greater health and social care costs.^8^

Current models of HIV care are not addressing the needs of people with HIV, with 47% of healthcare and 62% of social care needs not being met.^9^ Moreover, current care models may disadvantage older people living with HIV (OPWH) with, or at risk of, frailty as they can bounce between specialist HIV services and primary care. HIV specialist healthcare professionals (HCPs) often lack the awareness and experience to identify and manage frailty, and many general practitioners (GPs) lack knowledge and confidence around HIV.^10 11^ Use of multiple services can be especially challenging for some OPWH who avoid seeking care in non-HIV services because of perceived or experienced stigma and discrimination,^12^ which is often highlighted in community engagement work.^13–15^

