### Eligibility criteria

Inclusion and exclusion criteria are shown in table 1.

**Table 1 T1:** Inclusion and exclusion criteria

Inclusion criteria	Exclusion criteria
PLWH aged 50 years or older with evidence of frailty scoring 3+ on frailty screening, using the FRAIL scale^33^	PLWH aged under 50 or not defined as frail
Consent to contact the GP	Attended the Silver Clinic during the last 12 months

GP, general practitioner; PLWH, people living with HIV.

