### Recruitment

Eighty-four participants will be recruited from the RSCH. Potentially eligible individuals will be identified at their routine HIV annual health check attending the Lawson Unit in Brighton. The HIV annual health check takes place for all service users as part of usual care. The health check is performed by nurses and includes assessment of weight, blood pressure, urinalysis, mental health assessment, sexual health screening, adherence review and cervical cytology and contraception. During this assessment, patients 50 years and over will be screened for frailty using the FRAIL scale.^33^ Those with evidence of frailty on their screening will then be informed of the study and if they express an interest in participating will then be put in contact with the research assistant or nurse to explain the full details of the study, answer any questions and to give informed consent (see online supplemental material). Participants will be consecutively enrolled during the period of recruitment. Recruitment commenced October 2021 and will continue until March 2023, the study is expected to be completed by October 2023.

10.1136/bmjopen-2022-070590.supp1Supplementary data

For those that decline to take part in the study they will be provided with an information leaflet about frailty and their physician will be informed about the frailty screening we have done as part of their HIV usual care. Their HIV clinician can refer them to the Silver Clinic as per normal pathways once the feasibility study is complete. These patients will also be asked whether they are happy to share their reasons for declining and if so their answers will be recorded.

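### As printed, the age strata for randomisation skip ages 57–65, so stratified allocation is undefined for an eligible group; the first band is probably a misprint for 50–65

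*Protocol article*

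**What the plan says.** Three parts of the protocol article bear on this.

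- **Randomisation and blinding.** After the baseline assessment, "the research assistant will randomise participants using REDCap in a 1:1 allocation", "stratifying one age (50–56, 66–80, 81–95 and 96–110) and sex to ensure a balanced sample in both arms".
- **Eligibility criteria (Table 1).** The inclusion criterion is "PLWH aged 50 years or older with evidence of frailty scoring 3+ on frailty screening". The matching exclusion is "PLWH aged under 50 or not defined as frail". There is no upper age limit, and no age from 50 upwards is excluded.
- **Recruitment.** At the annual health check, "patients 50 years and over will be screened for frailty using the FRAIL scale". Screening therefore covers the same age range as eligibility.

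No section of the article says which stratum a participant aged 57 to 65 belongs to.

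**The concern.** Age bands used for stratified randomisation should place every eligible person in exactly one stratum. Here the list jumps from 56 to 66. Someone aged 60 can be screened, found eligible, consented and assessed at baseline, and then has no stratum from which to be allocated.

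If the allocation table were built as printed, three things could happen: the system refuses the allocation, staff choose a neighbouring band, or the person is allocated outside the stratification. In each case the age balance that the stratification is meant to secure is no longer guaranteed for this group, and the allocation procedure cannot be reproduced from the protocol.

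The gap also falls within the population that motivates the trial. The Introduction argues from the observation that "Studies including a younger cohort of PLWH aged 50–64 demonstrate a frailty prevalence comparable to that of HIV negative cohorts aged 65 and older". Ages 57 to 64, which are 8 of the 15 single-year ages in 50–64, have no stratum. How participants experience the trial processes, randomisation included, is one of the main objectives, so the randomisation rule handed on to a definitive trial should be one that can be applied.

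**Working it through.** **Inputs**

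- Eligible ages: 50 and over (Table 1). The check uses whole years from 50 to 110, the top of the highest printed band.
- Printed bands: 50–56, 66–80, 81–95, 96–110 (Randomisation and blinding).
- Sample size: at least 35 per arm, inflated for 15% attrition to 42 per arm and 84 in all (Sample size).

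**Step 1. The plan's own figure.** The article states that "a sample size of at least 35 participants per arm is recommended". Inflating for attrition gives 35 / (1 − 0.15) = 41.2, rounded up to 42 per arm, and 2 × 42 = 84. The stated sample size reproduces exactly. The point about the strata does not depend on it.

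**Step 2. Coverage of the printed bands.** Width = upper limit − lower limit + 1.

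- 50–56: 7 years
- 66–80: 15 years
- 81–95: 15 years
- 96–110: 15 years

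The total covered is 7 + 15 + 15 + 15 = 52 single-year ages. From 50 to 110 there are 110 − 50 + 1 = 61. The difference is 61 − 52 = 9. Checking each age in turn gives the uncovered ages as 57, 58, 59, 60, 61, 62, 63, 64 and 65.

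**Step 3. The likely intended first band.** The other three bands are contiguous and 15 years wide, while the first is 7. If it is read as 50–65, its width is 16, the total covered is 16 + 15 + 15 + 15 = 61, and no age from 50 to 110 is left out. The printed 56 is 65 with its digits swapped. The same clause contains another slip, where "one age" stands for what must be on age.

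**Step 4. Size.** The only age information is that 54% of a cohort of 2450 are over 50, that is 0.54 × 2450 = 1323 people. There is no finer breakdown, either for the cohort or for those who screen as frail. The number of the 84 who would be aged 57–65 therefore cannot be derived.

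**The case against.** The strongest reply is that this is a typographical error in a journal article and nothing more. The digits look transposed, the clause has a second slip, and the working table in REDCap may well hold 50–65. This stands as the likeliest explanation. It does not remove the point, because the bands are an operative randomisation rule, the printed rule cannot be applied to an eligible group, and only a look at the live table can settle the matter.

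A reader might also draw four stronger conclusions, none of which the article supports.

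- **That allocation actually failed.** The REDCap configuration is not shown. Even if it had the gap, a participant aged 57–65 might still have been randomised 1:1 without bias. What would be lost is defined stratification and a traceable account of the allocation.
- **That a large part of the sample is affected.** Without an age distribution, any percentage, or a claim that this is the largest age group, is a guess.
- **That the analysis is damaged.** The Analysis section plans descriptive summaries, proportions with confidence intervals and differences in means with confidence intervals. It names no analysis by age stratum and no adjustment for one. The primary outcomes (recruitment, retention and completion of measures) are feasibility measures, and recruitment would suffer only if a literal build blocked allocations.
- **That there are too many strata.** Four bands by sex gives 8 strata, an average of 84 / 8 = 10.5 people, and the 96–110 strata may well be empty. An empty stratum uses no allocations and does no harm. Merging the upper bands is a matter of preference, and changing the number of strata during recruitment would disturb a live scheme.

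**Conclusion.** The point holds for the scheme as written. The printed bands omit nine eligible single-year ages, 57 to 65, and the stated stratified allocation is undefined for anyone of those ages. This follows directly from setting the bands beside the eligibility criteria and needs no assumption.

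That the first band was meant to be 50–65 is an inference from the band widths and the swapped digits. It is probable, but the article does not say so. Whether the error exists outside the printed text, and how many participants it would touch, cannot be determined from the article. If the REDCap table is contiguous, the consequence is a correction to the text. If it is not, the trial needs a record of how the affected participants were allocated. No claim is made here about a stratum-adjusted analysis.

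**What to change.** 1. Check the age bands in the live REDCap allocation table.
2. Correct the first band to 50–65 in the protocol, so that the bands run without a gap from age 50. Correct REDCap as well if it has the same error.
3. If the live table had the gap, document how anyone aged 57–65 already randomised was allocated, including which stratum was used, if any. The article gives October 2021 as the start of recruitment, so such participants may exist.

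**Cost.** One check and a one-number correction to the text. If the live table is wrong, there is also a change to it and a short record of past allocations. Sample size, outcomes and planned analyses stay as they are. Collapsing the upper age bands is optional and forms no part of this correction; it could be considered for the definitive trial.

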### Analysis

#### Quantitative data

Baseline characteristics of the intervention and control participants will be summarised using descriptive statistics. Participant flow through the trial will be shown on a flow chart according to the Consolidated Standards of Reporting Trials (CONSORT) 2010^44^ statement extension for pilot and feasibility trials.^44^ Data will be presented by trial arm. Normally distributed variables will be summarised by their means and SD, skewed continuous variables by their medians and IQRs and categorical variables by their frequencies and percentages. For the feasibility outcomes, proportion of patients recruited, participants retained and data completeness 95% CIs will be presented. Differences in means between arms for the secondary outcomes will be presented with 95% CIs. Analysis will be of available cases following intention to treat principles. Missing data will be quantified but not imputed. A full statistical analysis plan will be agreed prior to database lock for the final analysis.

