### Objectives

The aim of this study is to assess the feasibility and acceptability of screening for frailty in OPWH and the Silver Clinic intervention, using a CGA approach; and to test the feasibility of a randomised controlled trial (RCT) to evaluate this intervention in the wider HIV setting. The main objectives are (1) to determine a sample size and primary outcome for a definitive RCT and (2) to explore what frailty means, what outcomes matter and the experience of the trial processes for OPWH, including communication about the trial, recruitment, randomisation, completion of measures and experience of participation in the trial. Secondary objectives are to (3) to undertake preliminary cost/service utilisation analysis and establish cost analysis outcomes for a definitive trial; (4) evaluate the feasibility and acceptability of implementing frailty screening and the Silver Clinic as part of HIV care; (5) to identify development needs and changes required to optimise the referral pathways, clinic structures and the intervention in preparation for a definitive trial and (6) to explore the acceptability of measures of frailty for OPWH. The objectives of the health economic analysis are: (1) to estimate the costs of the intervention; (2) to understand and estimate the costs of formal health and social care and informal care among patients with HIV and frailty and (3) to examine the feasibility of conducting cost-effectiveness analysis of this intervention in the full trial.

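### Secondary outcomes: the stated difference in means names no adjustment for baseline value, age or sex, so its intervals may be wider than the collected data allow (minor)

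*Protocol article*

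**What the plan says.** The Quantitative data section gives one between-arm estimate for the secondary outcomes: "Differences in means between arms for the secondary outcomes will be presented with 95% CIs". The same paragraph fixes the analysis set as available cases, rules out imputation, and says that a full SAP will be agreed before database lock. It mentions no covariate and no model, and it does not call the difference either adjusted or unadjusted.

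Three other places bear on this:

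- **Data collection:** the outcome measures are "collected at baseline, week 26 and week 52 postrandomisation". Table 2 marks all patient-reported outcomes at Day 0.
- **Randomisation and blinding:** participants are randomised after the baseline assessment, so the baseline values precede allocation. Allocation is stratified by age band "and sex to ensure a balanced sample in both arms".
- **Objectives:** the first main objective is "to determine a sample size and primary outcome for a definitive RCT". The Sample size section says that the trial's data will inform that calculation and speaks of estimating the SD.

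**The concern.** The paragraph summarises data by arm, then gives the difference in means, then fixes the analysis set and missing-data handling. With no covariate named, the sentence is easily carried out as a plain two-sample comparison of follow-up means. That would leave unused the baseline value of each outcome, which is often its best predictor and is already collected.

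Two things are at stake. The first is precision: a baseline-adjusted interval is narrower whenever baseline and follow-up are appreciably correlated. The second is chance imbalance. Stratifying by age and sex does not balance baseline HIV PROM, ASCOT or EuroQol scores, and with arms of this size those can differ noticeably.

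There is also a link to the first main objective. If the definitive trial is analysed with baseline adjustment, its sample size depends on the correlation as well as the SD. This article does not say that the correlation will be reported.

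**Working it through.** **Inputs from the article**

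- Evaluable number per arm: 35 ("a sample size of at least 35 participants per arm is recommended").
- Recruitment: 42 per arm, 84 in all, with 15% attrition ("we anticipate recruiting 42 patients per arm, that is, 84 in all allowing for attrition of 15% to be achievable").
- Allocation 1:1; confidence level 95%.
- Table 3 green thresholds for retention: at least 70 participants at 6 months and 55 at 12 months.

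**Assumption:** the baseline to follow-up correlation r. The article gives none, so a range is shown.

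**Step 1. Reproduce the plan's own figure.** 35/(1 − 0.15) = 41.2, rounded up to 42 per arm, or 84 in total. This matches. The figure rests on estimating an SD and not on comparing arms, so nothing below changes it.

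**Step 2. Unadjusted interval.** With n per arm, the half-width in SD units is t(0.975, 2n − 2) × √(2/n). For n = 35 this is 0.477 SD.

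**Step 3. Adjusted interval.** With k covariates, of which only the baseline value is assumed to explain outcome variation, the half-width is approximately

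t(0.975, 2n − 2 − k) × √[(2/n)(1 − r²)(1 + k/(2n − 3 − k))].

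The last factor is the cost of estimating the covariate effects. Two cases are shown: baseline only (k = 1), and baseline plus sex plus two age indicators that explain nothing further (k = 4). Baseline, sex and continuous age (k = 3) lies between them.

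| r | k = 1 | k = 4 | narrower than 0.477 by |
|---|---|---|---|
| 0.3 | 0.459 | 0.470 | 2-4% |
| 0.5 | 0.416 | 0.426 | 11-13% |
| 0.6 | 0.385 | 0.394 | 17-19% |
| 0.7 | 0.343 | 0.352 | 26-28% |
| 0.8 | 0.288 | 0.295 | 38-40% |

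**Step 4. At 12 months.** With 55 retained (27.5 per arm), the unadjusted half-width is 0.541 SD. At r = 0.5 adjustment gives 0.473 to 0.489 SD, 10-13% narrower. At r = 0.3 it gives 0.521 to 0.538 SD, a gain of 4% at most.

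**Step 5. Chance imbalance.** The standard error of a baseline difference at 35 per arm is √(2/35) = 0.239 SD, so its 95% range is about ±1.96 × 0.239 = ±0.47 SD. Given a baseline imbalance of d SD, the unadjusted follow-up difference shifts by about r × d. At r = 0.5 and d = 0.47 the shift is about 0.23 SD. Adjusting for baseline removes it, if the relation is roughly linear.

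**The case against.** The strongest objection is that the article does not say that the differences will be unadjusted. An ANCOVA estimate is also a difference in means with a 95% interval, and covariates for secondary outcomes are commonly left to the SAP, which is announced and not shown. This stands against any claim that the plan has chosen to ignore baseline. What remains is that the one sentence describing the estimate leaves out an improvement available at almost no cost.

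A second objection is that no decision in this trial turns on these intervals. The article says: "This is a feasibility trial, and therefore, not powered to test effectiveness of the intervention compared with standard treatment". The quantitative analysis plans no hypothesis test, and no row of Table 3 uses a between-arm difference. This stands and limits the severity.

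The text does not support three stronger readings that a reader might infer:

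- **That intervals ignoring the stratification are invalid.** Under randomisation the unadjusted difference is unbiased, and its interval already allows for chance imbalance. Leaving out stratification factors makes it conservative at worst, and the stratification itself limits imbalance in age and sex.
- **That the definitive sample size will be inflated.** Planning a baseline-adjusted trial from the raw SD alone would overstate the number by 1/(1 − r²), or 33% at r = 0.5. But the article does not say that only the raw SD will be used, and the correlation can be computed from the collected data whichever difference is reported.
- **That a QALY comparison is left unadjusted.** The article never mentions QALYs. It describes only tentative, non-conclusive cost-effectiveness ratios.

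The gain also depends on r and is small at 0.3. Service-use data from the CSRI may be skewed, so the calculation should not be carried over to every secondary outcome.

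**Conclusion.** The point holds as a minor improvement. No adjustment is stated, valid pre-randomisation covariates are collected, and using them would usually tighten the intervals. At 35 evaluable per arm, the half-width would fall from 0.477 SD to about 0.42 SD at r = 0.5 and 0.34 to 0.35 SD at r = 0.7, with little change at r = 0.3. These figures assume the stated correlations, equal arms, a roughly linear relation between baseline and follow-up, and age and sex adding nothing further. If age or sex does predict the outcome, the gain would be larger. The recruitment target, the progression criteria and the validity of the planned intervals are unaffected.

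**What to change.** In the SAP, before database lock, state for the continuous secondary outcomes that:

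1. Each between-arm difference in means is estimated by ANCOVA, or by a mixed model over weeks 26 and 52, adjusted for that outcome's baseline value, age and sex.
2. Age enters as a continuous covariate. The printed stratification bands leave out ages 57 to 65, so the bands cannot serve as a covariate until that gap is reconciled.
3. The unadjusted difference is reported alongside.
4. The SD and the baseline to follow-up correlation are reported with confidence intervals, as inputs to the definitive sample size.

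The cost is a few sentences. No new data, visits or participants are needed. The adjustment uses up to four degrees of freedom, which the k = 4 column already counts.
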